#### Statistical analysis

Statistical analysis of all data will be performed by a dedicated statistician in a blinded manner. All statistical analyses of the data will be performed using the SAS 6.12 (SAS Institute Inc., Cary, NC, USA) software.

The analysis data set will consist of a full analysis set (FAS), a per-protocol set (PPS), and a safety set (SS). FAS: according to the principle of analysis for intention to treat (ITT), participants will be rejected by the smallest and reasonable method. The last observation carried forward (LOCF) method will be used for the missing data supplement. The PP data set will include only participants who adhered to the study protocol and completed the clinical study. The minimum compliance rate for participants taking the investigational drugs in the PP data set is 80%. The SS will include information on safety records, including adverse events and laboratory test results. Quantitative indices recorded will include the numbers of cases, mean ± SD, median, and maximum and minimum values; qualitative or grade indices will be recorded using frequency and percentage. Two-sided tests will be used in all cases, and *P* ≤ 0.05 will be considered to be statistically significant.

From baseline to each time point, discrete variables will be described with frequencies and percentages, and continuous variables will be described with either mean and standard deviation for data with normal distribution or median and interquartile range for non-normally distributed data. For comparisons between the experimental and control groups at each time point, a chi-square test or Fisher’s exact test will be used for discrete variables, and Student’s *t* test or the Wilcoxon-Mann-Whitney *U* test will be used for continuous variables.

The analysis of concomitant medications will be analyzed by the chi-square test or Fisher’s exact test. The analysis of treatment compliance should include both the experimental drug and the basic treatment, and the chi-square test/Fisher exact probability method will be used for comparison.

All adverse events during the trial should be described in the form with the type, severity, and relationship with the experimental drug. Adverse events will be classified into all adverse events and related adverse events, among which, for conservative consideration, will include “definitely related,” “probably related,” “possibly related,” and “suspected related” to the drug.

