Occasionally, oral or intravenous BBR may cause adverse reactions such as nausea, vomiting, constipation, hypertension, respiratory failure, and paresthesias. Rare adverse effects including headache, skin irritation, facial flushing, headache, and bradycardia have also been reported [20]. The therapeutic dose of BBR (0.5 g) is generally safe and well-tolerated, and gastrointestinal reactions are most often caused by overdose (≥ 4 g).

A recent systematic review and meta-analysis demonstrated that BBR could significantly reduce the levels of TC, LDL-C, and TG in patients with dyslipidemia [13]. Unfortunately, these studies were limited by their high heterogeneity and high risk of biases. Kong et al. [17] proved that BBR treatment significantly improved lipid profiles; however, the randomization, blinding procedure, sample size calculation, and detailed inclusion and exclusion criteria have not been mentioned, and a lack of restriction on the other medications could have influenced the results. As there has been a lack of large-scale, high-quality randomized controlled trials on this possibility at the population level, this randomized, double-blind, placebo-controlled clinical trial was designed to determine the lipid-lowering efficacy and safety of BBR in treating dyslipidemia.

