### Outcomes

#### Primary outcome

The primary outcome is the percentage change in LDL-C from baseline at week 12.

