#### Secondary outcomes

The following are the secondary outcomes:
Lipid profiles: TC, TG, HDL-C, and LDL-C will be measured at baseline (visit 1) and weeks 4 (visit 2), 8 (visit 3), and 12 (visit 4).Hs-CRP, BP, and body weight will be measured at baseline (visit 1) and weeks 4 (visit 2), 8 (visit 3), and 12 (visit 4).BSC: the participants will be asked “which type of stool they have” at each visit during the treatment period.TCM symptom form (according to the Clinical Research Guidance of New Investigational Drug in TCM [25]) will be evaluated at baseline (visit 1) and weeks 4 (visit 2), 8 (visit 3), and 12 (visit 4).Adipokine profiles [fibroblast growth factor 21 (FGF21), adiponectin (APN), hormone-sensitive lipase (HSL)] will be assessed based on the blood specimens collected at baseline (visit 1) and week 12 (visit 4).Intestinal microbiota will be analyzed by the metagenomics based on the stool specimens collected at baseline (visit 1) and week 12 (visit 4).

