#### Sample size calculation

The sample size for this trial was calculated based on the primary outcome using the PASS 11.0 (NCSS LLC, Kaysville, UT, USA) software. According to the previous results of berberine on dyslipidemia [17, 26], the percentage reduction in LDL-C (the primary outcome) is 25% in the berberine group and 5% in the placebo group. Forty-seven patients in each group can achieve 80% power and rule out type I error of 5% by using a two-sided test. We expect that 20% of the participants may be lost to follow-up. Therefore, the sample size in each group should be adjusted to 59. In total, 118 participants will be enrolled in this trial.

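### Last observation carried forward is the only rule for missing LDL-C with 20% loss expected, so the week-12 estimate depends on when and in which arm participants leave

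*Protocol article*

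**What the plan says.** In the protocol article, the Primary outcome section states: "The primary outcome is the percentage change in LDL-C from baseline at week 12". Under Secondary outcomes, lipids are scheduled at four visits: "TC, TG, HDL-C, and LDL-C will be measured at baseline (visit 1) and weeks 4 (visit 2), 8 (visit 3), and 12 (visit 4"). Table 1 shows the same schedule.

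The Statistical analysis section defines the full analysis set: "according to the principle of analysis for intention to treat (ITT), participants will be rejected by the smallest and reasonable method". The next sentence is the whole missing-data rule: "The last observation carried forward (LOCF) method will be used for the missing data supplement". Groups are compared separately at each time point: "Student’s *t* test or the Wilcoxon-Mann-Whitney *U* test will be used for continuous variables". No longitudinal model, imputation model or sensitivity analysis for missing data is named. A per-protocol set of compliant completers is also defined.

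The Sample size calculation assumes that "the percentage reduction in LDL-C (the primary outcome) is 25% in the berberine group and 5% in the placebo group" and adds: "We expect that 20% of the participants may be lost to follow-up".

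**The concern.** LOCF assumes that a participant's LDL-C stays where it was at the last visit attended. For someone lost before week 4 the last value is baseline, so the primary outcome becomes exactly 0% change. For someone lost after week 4 or week 8, the value reached by then stands in for week 12. The primary estimate therefore mixes week-12 data with data from weeks 0, 4 and 8, in proportions set by the timing of dropout in each arm.

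The choice is stated outright, so it is not a detail left to an analysis plan. It acts directly on the primary result, and the expected loss is large enough to matter. The article's Discussion faults earlier berberine trials for incomplete outcome data and attrition bias, and this rule leaves the new trial open to the same criticism. The visits needed for a better analysis are already scheduled.

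**Working it through.** **The plan's own figure.** 47/(1 − 0.20) = 58.75, so 59 per arm and 118 in total, as stated. Expected loss is 0.20 × 59 = 11.8, about 12 per arm. (How 47 was reached is a separate question.)

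**Inputs.** From the Sample size calculation: mean reductions of 25% and 5%, and 20% loss. Assumed, because the article gives none: the course of the effect over visits, the timing of dropout, its split between arms, the SD and the correlation between visits.

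**Equal loss d = 0.20, same timing in both arms.** Let f4 and f8 be the fractions of the week-12 change reached at weeks 4 and 8.

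- All lost before week 4: 0.8 × 25 − 0.8 × 5 = 16.0.
- All lost after week 8: 20 × (0.8 + 0.2 × f8).
- Last visit spread evenly over baseline, week 4 and week 8: 20 × (0.8 + 0.2 × (0 + f4 + f8)/3).

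| Course of effect (f4, f8) | All before week 4 | Evenly spread | All after week 8 |
|---|---|---|---|
| Full by week 4 (1, 1) | 16.0 | 18.7 | 20.0 |
| Early (0.60, 0.85) | 16.0 | 17.9 | 19.4 |
| Linear (1/3, 2/3) | 16.0 | 17.3 | 18.7 |

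**Two possible targets.** The on-treatment difference is 25 − 5 = 20. If people off drug return to the placebo mean, the effect of assignment is 0.8 × 25 + 0.2 × 5 − 5 = 16. With evenly spread loss, LOCF falls 1.3 to 2.7 points below the first and 1.3 to 2.7 points above the second.

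**Unequal loss, illustrative only: 30% on berberine and 10% on placebo.**

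- All before week 4: 0.7 × 25 − 0.9 × 5 = 13.0. All after week 8 with full effect: 20.
- Timing differing between arms: 0.7 × 25 − 5 = 12.5 (berberine early, placebo late) and 25 − 0.9 × 5 = 20.5 (the reverse).
- Effect of assignment: 0.7 × 25 + 0.3 × 5 − 5 = 14.

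**Simulation.** 59 per arm, 1,500 runs per scenario, visit correlation 0.6, SD 20 or 34.6 points. At SD 34.6, 47 per arm gives 80% power for a 20-point difference in means. The true week-12 on-treatment difference is 20.

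- A likelihood estimate using weeks 4, 8 and 12 averaged 19.7 to 20.3 in every scenario, all of them missing completely at random or missing at random.
- With equal random dropout, the LOCF 95% interval covered 20 in 89–92% of runs at SD 20 and 93–94% at SD 34.6. With more loss on berberine, coverage was 75–89% and 89–93%.
- At SD 20 the LOCF standard error was 3.6 to 4.0, against a sampling SD of about 4.0 to 4.2 for the likelihood estimate, or 5–13% smaller. A rough check agrees: √(47/59) = 0.89.
- The LOCF standard error is close to the sampling SD of the LOCF estimate itself (for example 3.65 and 3.65 with the early course and random dropout). The undercoverage therefore comes mainly from bias.
- With no true difference and equal random dropout, rejection was 4.5–5.1%. With both arms falling 15% and more loss on berberine, the estimate moved by about 1.7 to 1.8 points against berberine and rejection was 6–7%.

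**The case against.** The strongest defence is that every bias figure rests on unstated trajectories and dropout patterns. With equal, evenly spread loss, the shift is only 1.3 to 2.7 points towards no difference, and the type I error is close to nominal. The per-protocol completers give a visible comparison, and further sensitivity analyses are commonly left to an analysis plan that is not shown here. All of this is fair. It limits the size of the point but does not rescue the rule: LOCF is stated as the method, and the completer set does not handle missing data.

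Four stronger readings are tempting and are not supported.

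- *Berberine will lose more participants because of gastrointestinal reactions.* The Background does say that "oral or intravenous BBR may cause adverse reactions such as nausea, vomiting, constipation", but the sentence opens by calling such reactions occasional. The same paragraph describes the therapeutic dose as generally well tolerated and ties gastrointestinal reactions mostly to overdose. The article neither predicts nor excludes unequal loss, and the 30%/10% split is only an illustration.
- *Carried-forward values make the standard error wrong in itself.* It is small only relative to that of a proper week-12 estimate.
- *LOCF never matches a meaningful effect.* With equal loss it equals the effect of assignment (16) if all leave before week 4, and the on-treatment effect (20) if all leave late with the full effect reached. The fault is that the data decide which one, or what mixture, is reported.
- *A mixed model is simply the valid answer.* It is valid under missing at random and estimates about 20. Judged against an effect of assignment of 16 or 14, it would be about 4 or 6 points too high. A standard model of post-baseline change also drops anyone lost before week 4.

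**Conclusion.** The point stands as a poor stated choice on the primary outcome. Under the planned 25% and 5% and equal 20% loss with the same timing in both arms, LOCF reports between 16 and 20 points, and about 17.3 to 18.7 with evenly spread loss. The on-treatment difference is 20, and the effect of assignment is 16 if people off drug return to the placebo mean. That second figure also equates loss to follow-up with stopping the drug, which the article does not say.

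A reader might take 16 to 20, or 13 to 20 under 30%/10% loss, as limits. They are not, because they assume the same timing in both arms. With different timing the 30%/10% case runs from 12.5 to 20.5. Nor can a single direction of bias be claimed: it depends on the target effect, which the article does not name, and on dropout that has not yet been seen. That is the reason not to fix a rule whose result depends on the dropout pattern in this way.

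**What to change.** 1. Name the target effect at week 12: the effect of assignment whatever happens to treatment, or the effect had participants stayed on treatment.
2. Replace LOCF in the primary analysis with a repeated-measures likelihood model on LDL-C at weeks 4, 8 and 12. Include treatment by visit and the stratification factors used at randomisation, with the week-12 contrast as primary.
3. Keep baseline LDL-C in the model so that all randomised participants are included as assigned, either as a response or through multiple imputation. Multiple imputation of LDL-C, with the percentage change computed afterwards, keeps the endpoint exactly as defined.
4. State that the primary analysis is valid under missing at random. Add a reference-based multiple-imputation sensitivity analysis (return to the placebo mean) for departures from it.
5. Keep LOCF at most as a sensitivity analysis.

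The sample size stays at 118 and no visit or measurement is added. The cost is revised analysis text, modest programming and an explicit reliance on missing at random. The article describes the trial as still recruiting; the change should be fixed before unblinding.

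### One P ≤ 0.05 significance label covers every between-group test, including about 32 secondary comparisons and the metagenomic outcome

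*Protocol article*

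**What the plan says.** The protocol article has one primary endpoint: "The primary outcome is the percentage change in LDL-C from baseline at week 12". The Sample size calculation section ties its two-sided 5% type I error to that endpoint.

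The Statistical analysis section does not keep this separation. It states "Two-sided tests will be used in all cases", and the same sentence continues that a P value at or below "0.05 will be considered to be statistically significant". It then assigns two-sample tests "For comparisons between the experimental and control groups at each time point". No outcome is set apart as primary, and none is described as exploratory or adjusted.

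The Secondary outcomes section lists what falls under this rule:

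- four lipids, hs-CRP, blood pressure, body weight and the TCM symptom form at weeks 4, 8 and 12;
- the Bristol Stool Chart, asked "at each visit during the treatment period";
- three adipokines at week 12;
- microbiota, with samples at baseline and week 12: "Intestinal microbiota will be analyzed by the metagenomics based on the stool specimens".

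**The concern.** This is a rule that the article states, not a detail that it leaves out. As worded, it gives a week-4 body-weight difference, a week-12 adipokine difference and the primary LDL-C result the same label at the same threshold. For a few secondary outcomes that is a familiar looseness. For metagenomics it is not a workable rule, because such data usually yield many features and a per-feature threshold of 0.05 labels about 5% of the unaffected ones as effects.

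At stake is how the secondary results are read. The Discussion says that blood and stool samples are kept to explore how berberine may lower lipids. Chance findings among bacteria, pathways or biomarkers could therefore enter that account as significant effects.

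**Working it through.** **The plan's own figure.** The article gives no error rate across outcomes. Its only type I error figure is the 5% for the primary test, which is one endpoint at one time point and needs no correction.

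**Count of conventional secondary comparisons** (Secondary outcomes section; post-baseline visits only):

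| Outcome | Tests |
|---|---|
| TC, TG, HDL-C at 3 visits | 9 |
| LDL-C at weeks 4 and 8 (week 12 is primary) | 2 |
| hs-CRP at 3 visits | 3 |
| Systolic and diastolic pressure at 3 visits (split assumed) | 6 |
| Body weight at 3 visits | 3 |
| Bristol Stool Chart at 3 visits | 3 |
| TCM form at 3 visits (one total score assumed) | 3 |
| FGF21, APN, HSL at week 12 | 3 |
| **Total** | **32** |

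Treating blood pressure as one variable gives 32 − 3 = 29. Counting week-12 LDL-C again as a secondary outcome gives 33. Tests on concomitant medication and compliance, and any repeat in the per-protocol set, are left out.

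**Expected false positives if no outcome is affected.** 32 × 0.05 = 1.6. Correlation does not change this expectation.

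**Chance of at least one, independent tests.** 1 − 0.95^k:

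- k = 29: 77.4%
- k = 32: 80.6%
- k = 33: 81.6%

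For jointly normal test statistics, independence is the worst case (Šidák's inequality), so about 81% is a ceiling for 32 tests.

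**Chance of at least one, correlated tests.** The article gives no correlations, so these are assumed. The results come from 200,000 simulated sets of 32 two-sided z tests.

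| Correlation within an outcome across visits | Correlation between outcomes | At least one false positive |
|---|---|---|
| 0.5 | 0 | 77% |
| 0.7 | 0 | 72% |
| 0.5 | 0.2 | 72% |
| 0.7 | 0.2 | 68% |
| 0.7 | 0.3 | 63% |
| 0.8 | 0.3 | 60% |
| 0.9 | 0.5 | 45% |

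With a within-outcome correlation of at least 0.7 and a between-outcome correlation of at least 0.2, the range is 45% to 68%. The mean number of false positives stays at about 1.6 in every row.

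**Without the lipids.** The trial expects real lipid effects, so the 11 lipid tests are poor candidates for true nulls. The other 32 − 11 = 21 tests give 21 × 0.05 = 1.05 expected false positives. The chance of at least one is 1 − 0.95^21 = 66% under independence and 54% at correlations of 0.7 and 0.2.

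**Metagenomics.** The number of features is an assumption. If none truly differs and each is tested at 0.05, 100 features give 100 × 0.05 = 5 and 500 give 500 × 0.05 = 25 declared by chance.

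**The case against.** The strongest reply is that multiplicity control for secondary and omics outcomes normally sits in the statistical analysis plan, which is not shown, so its absence proves nothing. In addition, the words about all cases grammatically govern two-sidedness, and nothing says that the P values are unadjusted. This stands in part: the mere absence of an adjustment is no finding. But the threshold follows in the same sentence without restriction, and the between-group tests are then set for each time point. An analysis plan that controlled the false discovery rate would have to qualify this published rule.

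A reader might go further and infer that false positives are almost guaranteed. The documents do not support that. For the conventional outcomes, 81% is a ceiling that needs independent tests and no true effect on anything, including lipids, where effects are expected. Near-certainty arises only if many metagenomic features are added and tested one by one at 0.05, and the article states neither their number nor such a test.

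It is also fair to say that the article claims no confirmatory status for secondary results and speaks of exploring a mechanism. That language supports labelling these results as exploratory; it does not support calling them significant at the primary threshold. Holm adjustment, or testing only week 12, is a legitimate choice for the conventional outcomes but a trade-off, and neither is required here.

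**Conclusion.** The concern holds in limited form. The significance label is too broad: as written it covers about 32 conventional secondary comparisons and the metagenomic outcome. Under no true effect the conventional comparisons yield 1.6 false positives on average. At least one is likely in most of the settings tried but not certain: at most 81%, and 45% to 77% over all the correlations assumed. The microbiota figure of 5 to 25 rests wholly on an assumed 100 to 500 null features and feature-by-feature testing, but the principle does not depend on the exact number.

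A reader might also infer that the trial's main conclusion is compromised. It is not: there is one primary endpoint at one time point, with a two-sided 5% level. What is affected is the reading of secondary and mechanistic results.

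**What to change.** Before unblinding, change the wording of the analysis section, and of the statistical analysis plan to match, as follows:

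- Limit the P ≤ 0.05 declaration of significance to the primary outcome, percentage change in LDL-C at week 12.
- Declare differences in microbiota features only at a Benjamini-Hochberg false discovery rate of 5%, and state the set of features over which it is applied.
- Report the other secondary outcomes as between-group estimates with 95% confidence intervals, with any P values labelled nominal or exploratory.

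The cost is that fewer secondary and microbiota results can be called significant. The primary test keeps its 5% level, so 47 per group before and 59 after allowance for dropout are not affected by this change, and no visit, sample or procedure changes.

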**Methods/design:**

This is a randomized, double-blind, and placebo-controlled clinical trial. A total of 118 patients with dyslipidemia will be enrolled in this study and randomized into two groups at a ratio of 1:1. BBR or placebo will be taken orally for 12 weeks. The primary outcome is the percentage of low-density lipoprotein cholesterol reduction at week 12. Other outcome measures include changes in other lipid profiles, high sensitivity C-reactive protein, blood pressure, body weight, Bristol Stool Chart, traditional Chinese medicine symptom form, adipokine profiles, and metagenomics of intestinal microbiota. Safety assessment includes general physical examination, blood and urine routine test, liver and kidney function test, and adverse events.

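### Continuous secondary outcomes are given only an unadjusted two-sample test at each visit; on the natural reading this ignores baseline and costs precision where an outcome tracks its own baseline closely

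*Protocol article*

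**What the plan says.** Four places in the protocol article bear on this.

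- **Abstract, Methods/design.** The secondary outcomes are described as changes: "Other outcome measures include changes in other lipid profiles, high sensitivity C-reactive protein, blood pressure, body weight".
- **Secondary outcomes.** The same variables appear as measurements at visits, without the word change. For lipids: "TC, TG, HDL-C, and LDL-C will be measured at baseline (visit 1) and weeks 4 (visit 2), 8 (visit 3), and 12 (visit 4". For the next group: "Hs-CRP, BP, and body weight will be measured at baseline (visit 1", with the later visits following.
- **Primary outcome.** Here the reference to baseline is explicit: "The primary outcome is the percentage change in LDL-C from baseline at week 12".
- **Statistical analysis.** One rule covers all between-group efficacy comparisons. "For comparisons between the experimental and control groups at each time point", a chi-square or Fisher test is used for discrete variables, and a Student's "test or the Wilcoxon-Mann-Whitney *U* test will be used for continuous variables". It does not say whether the tested variable is the visit value or the change, and it names no covariate. The sentence before it opens "From baseline to each time point, discrete variables will be described with frequencies and percentages", but that sentence concerns description, not testing.

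**The concern.** The abstract's wording and the test rule do not obviously concern the same quantity. In the Outcomes section the authors wrote out a change from baseline for the primary outcome and did not do so for the secondary ones. Taken with a test applied at each time point, this makes a comparison of visit values the natural reading.

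For an outcome that varies widely between patients but little within a patient, such as body weight, most of the variance in a visit value was already present at baseline. A test that ignores baseline keeps all of that variance in its standard error. A null result on such an outcome would then say little about berberine. Even if changes are meant, the stated tests still leave the baseline out as a covariate.

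**Working it through.** **The plan's own figures.** No power is stated for any secondary outcome. The sample size, set on the primary outcome, reproduces:

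- A two-proportion formula with unpooled variance gives (1.960 + 0.842)² × (0.25 × 0.75 + 0.05 × 0.95) / 0.20² = 46.1, rounded up to 47 per arm.
- Allowing for 20% loss, 47 / 0.8 = 58.75, rounded up to 59 per arm.

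Both sizes are used below: 59 if everyone randomized is analysed (the full analysis set with carried-forward values), and 47 for the expected completers.

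**Inputs from the protocol.** 59 or 47 per arm, 1:1 allocation, two-sided 5%.

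**Assumed inputs (none is in the protocol).** Body weight: SD 12 kg, effect 2 kg. Blood pressure: SD 15 mmHg, effect 5 mmHg. Correlation r between baseline and follow-up: shown as a range. SD taken as equal at baseline and follow-up.

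**Formulas.** The SD that enters the test, with σ the SD of a visit value, is:

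- visit value: σ
- change from baseline: σ√(2(1 − r))
- baseline as covariate (ANCOVA): σ√(1 − r²)

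Power comes from the noncentral t distribution with noncentrality (effect / SD) × √(n/2).

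**Which analysis is more precise.** 2(1 − r) − (1 − r²) = (1 − r)², which is never negative, and 1 − r² never exceeds 1. So in large samples ANCOVA is at least as precise as either alternative at every r. The change score beats the visit value only when 2(1 − r) < 1, that is r > 0.5. At r = 0.3 its SD is 1.18σ, against 0.95σ for ANCOVA.

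**Body weight.** With 59 per arm the visit-value noncentrality is (2/12) × √29.5 = 0.905. At r = 0.90 the ANCOVA multiplier is √0.19 = 0.436, so the noncentrality is 0.905 / 0.436, about 2.08.

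| | Visit value | Change, r = 0.90 / 0.95 / 0.97 | ANCOVA, r = 0.90 / 0.95 / 0.97 |
|---|---|---|---|
| 59 per arm | 15% | 52 / 81 / 96% | 54 / 82 / 96% |
| 47 per arm | 13% | 43 / 72 / 90% | 45 / 73 / 91% |

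Under the same SD, the standard error of the chance difference in mean baseline weight at 59 per arm is 12 × √(2/59) = 2.2 kg, larger than the assumed 2 kg effect.

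**Blood pressure, 59 per arm.** The visit-value noncentrality is (5/15) × √29.5 = 1.81.

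| r | Visit value | Change | ANCOVA |
|---|---|---|---|
| 0.5 | 43% | 43% | 55% |
| 0.6 | 43% | 52% | 61% |
| 0.7 | 43% | 64% | 71% |
| 0.8 | 43% | 81% | 85% |

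**A large lipid effect.** For LDL-C with an assumed SD of 0.9 mmol/L and effect of 0.8 mmol/L, at 47 per arm, the visit-value test already has 99% power. Change gives 97% to nearly 100% for r from 0.4 to 0.7, and ANCOVA gives over 99%.

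**The case against.** The strongest reply is that the text never says visit values are tested. The same rule must also serve the primary outcome, which is a percentage change, so a comparison at a time point can mean a comparison of the change at that time point. Read with the abstract, that would remove any mismatch. This stands in part: the tested variable is left open, and visit values are an inference, though the natural one given how the Outcomes section is worded.

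A second reply is that a condensed article leaves derived variables and covariates to the analysis plan. That is fair for detail such as transformations. But the article does not leave the method open: it names unadjusted tests. On either reading they omit the baseline as a covariate, and an analysis plan that follows the article would inherit this.

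A third reply is that the size rests entirely on assumptions. That stands. No weight or blood pressure effect is hypothesised, and the sharp contrast for weight comes from a small effect (2/12 = 0.17 SD) and high correlations.

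A reader might also infer more than the document supports:

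- **That the secondary outcomes are formally defined as changes.** Only the abstract uses the word; the Secondary outcomes section does not.
- **That the comparison would be biased or invalid.** In a randomized trial a comparison of visit values is unbiased, and its standard error already allows for chance baseline differences.
- **That baseline variation would hide lipid effects generally.** The LDL-C illustration shows a large effect detected under every analysis.
- **That testing change alone would cure the problem.** It gains nothing at r = 0.5 and loses power below it.

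**Conclusion.** The point holds as one of precision and clarity for the continuous secondary outcomes. The abstract, the Secondary outcomes section and the Statistical analysis section do not together fix what is tested, and the tests named leave the baseline out as a covariate on any reading. If visit values are tested, the loss could be severe for body weight and moderate for blood pressure under the assumed values. It is small or absent for weakly correlated markers and for large lipid effects. Neither the validity of the comparisons nor the definition of the primary outcome is affected. The ordering of the three analyses follows from the formulas under equal baseline and follow-up SDs. The percentages depend on SDs, correlations and effects that the protocol does not give. The change is worth making because it is nearly free, not because the main conclusion is at risk.

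**What to change.** In the Statistical analysis section, state that each continuous secondary outcome is compared between groups at each post-baseline visit by ANCOVA, or by a mixed model over the visits, with that outcome's own visit 1 value as covariate. Analyse skewed markers such as TG and hs-CRP on the log scale. Report adjusted differences, or ratios for log-scale outcomes, with 95% confidence intervals.

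This also reconciles the three sections. If visit value = a + b × treatment + c × baseline, then subtracting baseline from both sides gives change = a + b × treatment + (c − 1) × baseline. The treatment effect b is the same whether the visit value or the change is modelled.

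Do not switch to unadjusted change scores alone, because these lose power when the correlation is below 0.5.

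The cost is analysis wording only. Table 1 already schedules lipids, hs-CRP, blood pressure, body weight and adipokines at visit 1, so no new data or visits are needed.
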